# Prevention of pneumococcal infections: Impact of structured medico-pharmaceutical collaborative management to improve vaccination coverage of at-risk patients (OPTIVACC study): Protocol for a multicenter randomized stepped -wedge study

**DOI:** 10.1016/j.conctc.2025.101462

**Published:** 2025-02-15

**Keywords:** Infectiology, Pneumococcal infections, Vaccination, Hospital pharmacy

## Abstract

**Background:**

*Streptococcus pneumoniae* causes infections especially in patients with immunodeficiency or specific comorbidities. Most could be avoided through pneumococcal vaccination (PV), but PV coverage is only 20 % in France. Many studies assess methods on vaccination coverage improvement, but none evaluates pharmacist-physician collaboration in hospital on PV coverage of inpatients at-risk of invasive pneumococcal disease (IPD).

**Methods:**

This study is a multicentric stepped-wedged randomized trial involving 12 units in 9 French hospitals (3 university and 6 local) during 4 periods of 90 days each. Three clusters will be made, each composed randomly of clinical and surgical units from one university hospital and clinical and surgical units of 2 local hospitals. For each period, one unit will have to include 16 non-vaccinated inpatients at risk of IPD. Patients in the control phase will receive usual care. During the interventional phase, the pharmacist will inform the physician on PV necessity, who will report recommendation and prescribe it at discharge. The pharmacist will perform a consultation and send a discharge letter to the patient's community pharmacist. The primary outcome will assess the impact of intervention on PV coverage after 6 months. Secondary outcomes will evaluate vaccines dispensing, uncompleted protocol rate and intervention process. A subgroup analysis between university and local hospitals and clinical and surgical units, respectively will be made.

**Discussion:**

This study will assess the impact of medico-pharmaceutical collaboration in hospital on PV coverage in inpatients at risk of IPD. Hospitalization could be a way to promote vaccination and enhance healthcare system performance.

**Trial registration:**

Clinicaltrials.gov, NCT05060146. Registered on September 16th, 2021.

## Background

1

*Streptococcus pneumoniae* (pneumococcus) is a cocci gram-positive bacterium which is responsible for invasive pneumococcal diseases (IPD) like meningitis and bacteremia or more common infections like otitis and community acquired pneumonia. In France, in 2020, pneumococcus was the first cause of bacteremia (5.2 cases/100,000 inhabitants) and meningitis (0.7 cases/100,000 inhabitants) [1]. It is also the main cause of bacterial pneumonia [2]. Children under 5 years old and elders are more likely to develop pneumococcal infections [1,3,4], but other populations are considered at risk, like adult patients with immunodeficiency or patients with some specific comorbidities (cardiac, renal, respiratory failure, diabetes, etc.) [5].

Pneumococcal infections are an economic burden for society. In Europe, all documented cases of pneumonia generate costs around €10 billion per year [6]. In France, the average hospitalization fee for a community acquired pneumococcal pneumonia is €7,293, the follow-up fee being €1241 [7]. Furthermore, the World Health Organization (WHO) included pneumococcus on a priority pathogens list for research and development of new antibiotics, because of the antibiotic resistance of the pathogen, especially against penicillin [8,9]. Pneumococcal pneumonia is also considered the evitable disease with the highest mortality rate [10], explaining that vaccination could be a major health issue.

In France, 2 vaccines against pneumococcus are available: 23-valent pneumococcal polysaccharidic vaccine (PPSV23) and a 13-valent pneumococcal conjugate vaccine (c) [11,12]. In 2017, the High Council for Public Health (HCPH) recommended a sequential vaccination with PCV13 followed by a shot of PPSV23 8 weeks later for all patients older than 5, considered at risk of pneumococcal infections [13,14]. For patients having received just one dose of VPP23, it is recommended to do a dose of PCV13 after 1 year.

Even if the prevention by vaccination seems to be a good solution in view of the economic cost of pneumococcal infections and the emergence of antibiotic resistance, the vaccine coverage is only about 20 % among the target population according to HCPH [14]. A study, conducted in France between 2014 and 2018 presents a rate of only 4.5 % of vaccinated at-risk patients and a decline of vaccination coverage in this period, while patients with chronic pathologies and healthcare visits increase [15]. Some of the main contributing factors include: lack of vaccination campaigns, difficulty in finding patient vaccination history, confusion about prescription and administration of the vaccine between healthcare professionals, lack of knowledge about vaccines among patients and recommendations from physicians, respectively [16,17].

Studies in Canada or the United states show that the pharmacist could promote the PV, both in pharmacies and hospitals for all vaccines. However, none of them were conducted in France, many of the studies are not randomized controlled studies and did not analyze the collaboration between pharmacist and physician [18,19].

The primary outcome of our study is to evaluate the impact of medico-pharmaceutic collaboration in hospital on the PV coverage for at-risk patients. The secondary outcomes are to investigate the rate of incomplete vaccination protocols, vaccines dispensation, multidisciplinary collaboration, as well as a subgroup analysis between different types of units (clinical vs surgical) and healthcare facilities (hospital vs university hospital). Clinical pharmacy practices and the degree of collaboration between caregivers may vary according to the type of service and facility. We want to analyze the collaborative management in different contexts in order to assess these potential differences.

## Methods

2

### Design

2.1

This study will be a multicentric prospective stepped wedge controlled randomized trial (SW-CRT) with 3 clusters and 4 periods. This design was chosen because it will not be possible to do an individual randomization of patients. Indeed, there would be a high risk of contamination bias as soon as the interventional strategy will take place in the unit with the medico-pharmaceutical collaboration: it will change the habits for all patients, including control patients. The cluster cross over will be in one direction only. A sequential permutation of each cluster from control to experimental period, determined by randomization, will be made after a set time of 90 days. All the clusters will start in the control phase and end up in the interventional phase. The study design is outlined in Fig. 1.

**Fig. 1 fig1:**
[figure not shown]
Study design.

### Settings/population

2.2

3 university hospitals and 6 local hospitals with clinical pharmacy activities in the region of Occitanie, France, have agreed to participate in this study. The 3 clusters will be made up of randomly selected hospitals and units. Each cluster comprises 4 units: 2 units (clinical and surgical) from the same university hospital and a clinical and surgical unit from different local hospitals. Hospital centers, units and number of patients to be included are described in Table 1. For this study, each unit will recruit 8 patients per period, so 64 patients during the period of inclusion. Therefore, a hospital will include 64 patients and a university hospital 128, totaling 768 patients for the entire study.

**Table 1 tbl1:** Hospital centers, units and number of patients to include.

Hospital center	Type of establishment	Unit	Unit type	Total number of patients to include
Nîmes	University hospital	General medicine	Clinical	64
		Digestive surgery	Surgical	64
Montpellier	University hospital	Internal medicine	Clinical	64
		Digestive surgery	Surgical	64
Toulouse	University hospital	Internal medicine	Clinical	64
		Vascular surgery	Surgical	64
Bagnols-sur-Cèze	Hospital	Gastroenterology	Clinical	64
Montauban	Hospital	Pneumology	Clinical	64
Saint-Gaudens	Hospital	General medicine	Clinical	64
Alès	Hospital	Surgery	Surgical	64
Perpignan	Hospital	Surgery	Surgical	64
Sète	Hospital	Surgery	Surgical	64

To qualify, patients must be over 18 years old and covered by the French National Health Insurance (NHI). They must be hospitalized in one of the units participating in this study and also need to be at risk of pneumococcal diseases and eligible to the pneumococcal vaccination according to the French high council of public health recommendations [14]. At admission, patients will receive medication reconciliation from the clinical pharmacist of the department. Patients requiring only a vaccine booster will not be included in the study. The vaccination status of the patient will be confirmed at least by 3 sources as recommended by French society of clinical pharmacy and high authority of health: patient or caregiver declaration, usual drugstore, patient's physician or medical records [20,21]. As last criteria, the patient will go back home at the end of hospitalization. The patient's consent will be obtained and recorded in the medical file, followed by regular monitoring visits carried out by a clinical research associate.

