### Sample size calculation

2.6

This study was designed according to a validated methodology of SW-CRT [23]. The Canadian meta-analysis from Taitel et al. suggests that the vaccine coverage risk ratio is 2,96 for intervention [19], but for this study, a less optimistic hypothesis was made.

Considering an intraclass correlation coefficient of 0.05, a power of 95 % and a two-sided alpha level of 5 %, a total of 684 patients must be included to highlight an absolute difference of 20 % between the control group (20 %) and the experimental group (40 %). Assuming 10 % of unusable data, the patient number were increased to 768, so 8 patients per unit and period.

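### Sections 2.2 and 2.6 state a quota of 8 patients per unit and period, which gives 384 patients; the planned 64 per unit and 768 in total need 16.

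*Protocol article*

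**What the plan says.** The article gives the recruitment quota per unit and period in three places.

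- Section 2.2 (Settings/population): "each unit will recruit 8 patients per period, so 64 patients during the period of inclusion".
- Section 2.6 (Sample size calculation): "the patient number were increased to 768, so 8 patients per unit and period".
- Abstract, Methods: "For each period, one unit will have to include 16 non-vaccinated inpatients at risk of IPD".

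The number of units and periods is stated consistently. The abstract describes a trial "involving 12 units in 9 French hospitals (3 university and 6 local) during 4 periods of 90 days each", and section 2.1 describes a "stepped wedge controlled randomized trial (SW-CRT) with 3 clusters and 4 periods". Section 2.2 adds that "Each cluster comprises 4 units", and 3 × 4 = 12 agrees with the 12 rows of Table 1.

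Table 1 gives a target of 64 for every unit. The text of section 2.2 says that "a hospital will include 64 patients and a university hospital 128, totaling 768 patients for the entire study".

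Section 2.6 requires 684 patients for 95% power at a two-sided alpha of 5%, with an intraclass correlation of 0.05 and vaccination rates of 20% against 40%. It then allows for 10% unusable data.

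**The concern.** Sections 2.2 and 2.6 each present the 8 as consistent with a larger figure (64 per unit, 768 overall), and in both places the multiplication fails by a factor of two. The abstract gives a different quota, so the article also contradicts itself.

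The number of patients per unit and period is the cell size of a stepped-wedge design and a direct input to its power. A reader who takes the cell size from the sample-size section arrives at a trial smaller than the one that section says is needed. The article is the public record of the planned design, and recruitment cannot be judged against plan if the Methods imply 384 in one phrase and 768 in another.

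**Working it through.** **Recruitment arithmetic**

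Inputs: 12 units (abstract, Table 1) and 4 periods (abstract, section 2.1), so 12 × 4 = 48 unit-periods.

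| Quota per unit and period | Per unit (× 4) | Total (× 48) |
|---|---|---|
| 8 (sections 2.2 and 2.6) | 32 | 384 |
| 16 (abstract) | 64 | 768 |

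Cross-checks on the targets:
- Table 1: 12 × 64 = 768.
- Per-hospital figures: 3 × 128 + 6 × 64 = 384 + 384 = 768.
- Back-calculation: 64 / 4 = 16.
- For 8 to give 64 per unit there would have to be 64 / 8 = 8 periods. The article describes no such design.

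**Reproducing the plan's 684 and 768**

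The outcome variance is not given. I assume the control-rate variance, v = 0.20 × 0.80 = 0.16, and treat the 3 clusters as the units of randomisation. The Hussey-Hughes variance of the treatment effect is

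Var = I·s²·(s² + T·τ²) / [(I·U − W)·s² + (U² + I·T·U − T·W − I·V)·τ²],

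with I = 3 clusters, T = 4 periods, τ² = ICC × v, s² = (1 − ICC) × v / m, and m patients per cluster-period. One cluster crosses over at each step, so:
- U = 3 + 2 + 1 = 6
- W = 0 + 1 + 4 + 9 = 14
- V = 9 + 4 + 1 = 14
- I·U − W = 18 − 14 = 4
- U² + I·T·U − T·W − I·V = 36 + 72 − 56 − 42 = 10
- τ² = 0.05 × 0.16 = 0.008

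Power = Φ(0.20 / √Var − 1.96).

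- m = 57: s² = 0.152 / 57 = 0.002667. Var = 0.008 × 0.034667 / 0.090667 = 0.003059. Power = 0.951. At m = 56 it is 0.948, so 57 is the smallest cell that reaches 95%, and 57 × 3 × 4 = 684, as stated.
- Allowing for 10% unusable data: 57 / 0.9 = 63.3, rounded up to 64 per cluster-period. Then 64 × 12 = 768, and 64 / 4 units = 16 per unit and period.

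The plan's own figures therefore lead to 16.

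**Power at a quota of 8**

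On the same basis, 8 per unit is 32 per cluster-period.

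- N = 384: s² = 0.152 / 32 = 0.00475. Var = 0.01425 × 0.03675 / 0.099 = 0.005290. Power = 0.785.
- N = 384 × 0.9 ≈ 346 (m = 28.8): power = 0.745.

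Because the variance is an assumption, the range is shown below. The value 0.20 is the average of 0.16 and 0.24; 0.21 is 0.30 × 0.70.

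| N | 3 clusters, v = 0.16 / 0.20 / 0.21 | 12 units, v = 0.16 / 0.20 / 0.21 |
|---|---|---|
| 684 | 0.951 / 0.899 / 0.884 | 0.967 / 0.924 / 0.911 |
| 384 | 0.785 / 0.691 / 0.670 | 0.834 / 0.746 / 0.725 |
| 346 | 0.745 / 0.649 / 0.627 | 0.799 / 0.706 / 0.685 |

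**Against actual recruitment**

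The Trial status section reports 646 inclusions: 646 / 48 = 13.5 per unit-period on average, above 8 and below 16.

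**The case against.** The strongest reply is that this is a reporting slip with no effect on the trial. The total, every row of Table 1, the per-hospital targets and the abstract's quota agree with one another, and only one derived number, printed twice, is wrong. The article appeared in February 2025, after inclusion closed in September 2023 and follow-up ended in March 2024, so no site could have recruited from this text. The full protocol that the sites used is not shown, and nothing indicates that it carried the 8. Most of this stands, and it limits the consequence. It does not remove the error, which sits in the recruitment and sample-size sections of the published design.

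Four stronger readings are tempting, and the document does not support them.

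- A reader might infer that units stopped at half the planned sample. The 646 inclusions exceed 384, so 8 was not applied as a uniform cap.
- A reader might take 646 as proof that 16 was the working target. An average of 13.5 is compatible with 16 but cannot confirm it. The support for 16 is the abstract and 64 / 4.
- A reader might set a power of 65% to 71% (346 patients, variance 0.20) against the stated 95%. That is not like for like, because with variance 0.20 even 684 patients give only about 90% (3 clusters) or 92% (12 units). Part of that gap comes from the variance and not from the 8.
- A reader might say that the sample size cannot be reproduced. It can, with one assumption about the variance. The obstacle is the unstated variance, not the 8.

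**Conclusion.** The point holds as an error in the stated design. The quota of 8 in sections 2.2 and 2.6 is wrong by a factor of two against the article's own units, periods, per-unit targets, per-hospital targets and total, and it contradicts the abstract. This part needs no assumption.

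The size in power terms does rest on assumptions. On the basis that reproduces 684 at 95% (Hussey-Hughes, 3 clusters, ICC 0.05, variance 0.16), a trial run at 8 per unit and period would have about 78% power before losses and about 75% after them. Across the variances and cluster definitions considered, the range is about 63% to 83%. Every variant falls well short of 95%. These figures describe the design that the Methods state, not the trial as it was conducted.

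**What to change.** In section 2.2 and in section 2.6, replace 8 patients per unit and period with 16. Then 16 × 4 = 64 per unit and 16 × 48 = 768 in total, and both sections agree with Table 1, the per-hospital targets and the abstract.

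The cost is an erratum of two numbers. The required sample size, the design, the analysis and the conduct of the trial do not change.

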### Intervention

2.4

During the control period, the patient management will be as usual: the pharmacist in the unit will do a medication reconciliation and check his pneumococcal vaccination status. If the patient is eligible for vaccination based on HCPH criteria [14] but not vaccinated according to three sources [20,21], the pharmacist will note it in the patient's medical record. During the month after discharge, the pharmacist of the unit will check pneumococcal vaccines prescription and notification of vaccination indication in the discharge letter by the department physician. Six months after the end of hospitalization, the coordinating pharmacist of the study will call the patient's usual community pharmacy to check vaccine dispensation. He will also call the patient's general practitioner and/or home care nurse to check the vaccine administration. Finally, the SNDS will be analyzed to check all vaccine dispensation.

Concerning the experimental stage, the pharmacist of the unit will also do medication reconciliation, check the vaccination status of patient and report it in the medical record. If it is negative, the pharmacist will communicate the vaccination benefit to the physician the vaccination benefit. Then the physician will suggest the pneumococcal vaccination and prescribe the protocol with patient agreement. He will note vaccination indication in the discharge letter for the GP. Before the patient returning home, the pharmacist will have a pharmaceutic discharge conversation with the patient and explain the benefits of vaccination and the protocol (dispensation and administration). The pharmacist will also send a pharmaceutic discharge letter to the patient's usual community pharmacy about pneumococcal vaccination. The follow-up procedure and the data collected will be the same for the two phases. For ethical reasons, the coordinating pharmacist will inform the GP of the recommendation to vaccinate all unvaccinated patients of the study at the end of their follow-up. The OPTIVACC study's flow of intervention is outlined in Fig. 2.

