### Blinding

2.5

This study is single-blind. Indeed, the patient will not know if he was included in control period or interventional period. However, due to intervention type and the study design, pharmacists and physicians of the participating units will know if the patient is included in observational or experimental stage because they must do or not the intervention.

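### Unit staff who know the phase and deliver the intervention also recruit the patients, so case mix may differ by phase; age and immune status belong in the primary model

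*Protocol article*

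**What the plan says.** - **Who knows the phase.** Blinding (2.5) says that "pharmacists and physicians of the participating units will know if the patient is included in observational or experimental stage", because they must carry out the intervention or withhold it.
- **Who finds the patients.** Under Settings/population (2.2) and Intervention (2.4), the clinical pharmacist of the unit does the medication reconciliation and checks vaccination status. The Discussion calls reconciliation the first step before inclusion.
- **How many.** Enrolment is by a fixed number per unit and period. The Abstract says "one unit will have to include 16 non-vaccinated inpatients at risk of IPD" in each period; sections 2.2 and 2.6 say 8.
- **Last criterion.** Section 2.2 ends its eligibility list with "As last criteria, the patient will go back home at the end of hospitalization". No time of assessment is given.
- **The offer.** In the experimental phase (2.4), once the pharmacist has spoken to the physician, "Then the physician will suggest the pneumococcal vaccination and prescribe the protocol with patient agreement". For the control phase the section describes only a note in the medical record.
- **Analysis.** Statistical analysis (2.8) uses a mixed logistic regression for the primary outcome. Age and immunocompromised status appear only in a possible sensitivity analysis by sequential adjustment, and the two age groups both contain age 65.
- **Status.** 646 patients were included by 13 September 2023, and follow-up ended on 14 March 2024.

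**The concern.** Randomising when clusters cross over balances the clusters' characteristics over time. It does not balance patients who are identified after the phase is known. The people who find candidates here also deliver the intervention, so they may recruit a different kind of patient once it is running, even without intent.

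Willingness to be vaccinated is the most sensitive characteristic, because it lies so close to the primary outcome of a complete protocol at six months. In the experimental phase staff learn the patient's answer during the stay. In the control phase the plan describes no comparable offer. If inclusion were settled after that answer, refusers could be under-represented in one phase only, and the treatment coefficient would absorb the difference.

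**Working it through.** **1. The plan's own figure.** Section 2.6 states that "a total of 684 patients must be included to highlight an absolute difference of 20" points (20% against 40%), with ICC 0.05, power 95% and two-sided alpha 5%. The Hussey-Hughes stepped-wedge variance is

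Var = I·s²·(s² + T·t²) / [(I·U − W)·s² + (U² + I·T·U − T·W − I·V)·t²]

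I is the number of clusters and T the number of periods. U is the number of exposed cluster-periods. W and V are the sums of squared column and row totals of the exposure matrix. t² is the between-cluster variance, and s² is the within-cluster variance divided by the cluster-period size m.

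Take I = 3, T = 4, U = 6, W = V = 14 and total variance 0.2 × 0.8 = 0.16. Then t² = 0.05 × 0.16 = 0.008. With m = 57, s² = 0.152/57 = 0.002667.

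- Var = 3 × 0.002667 × 0.034667 / (4 × 0.002667 + 10 × 0.008) = 0.003059, so SE = 0.0553.
- Power = Φ(0.20/0.0553 − 1.96) = 95.1%, and N = 3 × 4 × 57 = 684. With m = 56, power is 94.8%.

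The stated 684 is reproduced. The final target of 768 equals 12 units × 4 periods × 16. The figure of 8 per unit and period gives 384, so 8 and 16 need to be reconciled.

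**2. Size of a selection effect (assumed inputs).** The documents give no figure for this. Assume no true effect and the planned 20% completion among eligible patients in both phases. Let u be the share who would never be vaccinated, and e the fraction of these left out in the intervention phase only. The apparent intervention-phase rate is 0.20/(1 − u·e). With u = 0.4:

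| e | Share of all eligible left out (u·e) | Apparent rate | Spurious difference |
|---|---|---|---|
| 0.25 | 0.10 | 0.20/0.90 = 22.2% | +2.2 points |
| 0.50 | 0.20 | 0.20/0.80 = 25.0% | +5.0 points |
| 0.75 | 0.30 | 0.20/0.70 = 28.6% | +8.6 points |

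Over u from 0.2 to 0.6 and e from 0.1 to 0.75, the difference runs from +0.4 points (0.20/0.98) to +16.4 points (0.20/0.55).

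**3. Effect on the test.** Take the 12 units as clusters (U = 24, W = 224, V = 56) with the same variance components. SE is 0.0501 at 768 patients (m = 16) and 0.0541 at 646 (m = 646/48 = 13.46). The two-sided rejection rate under no effect with bias b is Φ(b/SE − 1.96) + Φ(−b/SE − 1.96).

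| Bias b | 768 patients | 646 patients |
|---|---|---|
| 0 | 5% | 5% |
| +2 points | 6.8% | 6.6% |
| +5 points | 17% | 15% |
| +8.6 points | 41% | 36% |

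Mimicking the whole 20-point effect would take heavy selection. Moderate selection would already disturb the test.

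**The case against.** The case against a strong reading is good, and most of it stands.

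- **The criterion concerns destination, not willingness.** It applies in both phases, and a patient who declines and goes home satisfies it. It can be read as an expectation held at inclusion. Reconciliation takes place at admission, and the Abstract puts the prescription at discharge, when the destination would normally be known. The flow figure, which might show the sequence, is not available here. A reader might infer that return home is settled only after the offer, or that refusers may be passed over. The text says neither.
- **No surplus is documented.** A reader might infer that units pick freely from a larger pool. No section says so. The Discussion calls recruitment a critical point, and 646 of 768 is 84% of the target, which argues against much surplus. A shortfall does not prove that nobody was left out, but it gives no support to free choice.
- **Consecutive inclusion, a screening log and the timing of consent or non-opposition** are details that an article commonly leaves to the full protocol. Their absence is no finding, and with enrolment closed they could not be introduced now.
- **The illustration rests wholly on assumed inputs**, as its wide range shows.

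What survives is that recruitment follows knowledge of the phase, by the staff who deliver the intervention, and that the plan treats its two named baseline variables as optional. That recruitment after allocation is common in open cluster trials does not remove the exposure.

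**Conclusion.** The point holds in limited form. The article itself establishes recruitment by staff who know the phase, so the phases may differ in case mix, and randomising cluster order does not prevent this. Selection on willingness is a possibility that the article neither rules out nor describes. The +2 to +9 points is not an estimate for this trial. It holds only if there is no true effect, completion is 20%, 40% of eligible patients would never be vaccinated, and the omissions occur in the intervention phase alone. The direction, in favour of the intervention, also follows from that scenario; other case-mix differences could act either way.

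The weakness that can still be corrected is in section 2.8: adjustment for age and immune status is only a potential sensitivity analysis, and its age groups overlap at 65.

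**What to change.** 1. Specify age and immunocompromised status as covariates in the primary mixed logistic model, and keep the model without them as the sensitivity analysis. Enter age preferably as continuous, which also removes the overlap at 65. Fix this before the outcome is analysed by phase. If that has already happened, label the adjusted model as post hoc.
2. Keep every included patient in the analysis set, whatever the final discharge destination.
3. Compare baseline characteristics and inclusion counts between the phases.
4. State as a limitation that adjustment deals only with measured case mix and cannot remove selection on unmeasured willingness.

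**Cost.** Almost nothing: section 2.8 already names both variables, and the comparison by phase is one descriptive table. The adjusted odds ratio is conditional on the covariates, so it will not match the unadjusted one exactly even without imbalance, and the report should say so. Patients who do not go home may complete less often, which could lower the rates slightly.
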